#### Data sets

For evaluation of security all data gathered will be used and analyzed as treated. The analysis of the efficacy measures, especially with respect to the stimulus placement, requires a concentration on patients treated per protocol (PP). Missing observations are imputed using a full conditional Markov-Chain Monte Carlo method for variables with more than 75% valid values. An exploratory analysis of all dependent variables by the randomised treatment, i. e. the mere intention to treat (ITT), will be conducted to plan subsequent confirmatory studies.

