### Sample size calculation

Effect size and dispersion were taken from our last study of TMS against tinnitus [34]. The ratios of tinnitus distress score after treatment to tinnitus distress score at baseline are assumed to follow normal distributions with standard deviation 0.18 after taking logarithms. A relevant effect size of 0.19 logarithmic units would arise from the ratio of geometric mean scores of 80% of baseline after efficacious stimulation to 97% after sham stimulation. All three pairwise group comparisons will be conducted. Therefore the probabilities of the errors of first and second kind are Bonferroni-adjusted to significance level 0.017 and power 0.93 locally to ensure multiple level 0.05 and multiple power 0.8. Consequently the planned number of patients to be included in the study is 48, i. e. 16 in each arm. A closed testing procedure preserves the multiple significance level and power while treatments are compared at different points in time.

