### Data analysis

The geometric mean tinnitus score (TQ) in percent baseline will be compared between the three groups after the full treatment course of 4 weeks after the first stimulation, after 6 weeks, as well as 28 and 56 weeks after the first cTBS treatment in that prespecified order, as we expect effects sizes to have that order. If one group comparison is not statistically significant, the following comparisons are rated as not significant too. The confidence intervals for ratios of geometric means of tinnitus scores at 4 and 6 weeks will be computed from an analysis of variance (ANOVA) with factors *group *(SAC, TAC, PLC) and *time *(4 and 6 weeks) and the *group*time *interaction. Further ANOVAs of TQ with the between subject factor *group *will be carried out after 8, 28, and 56 weeks after the first treatment. Their residual variances are expected to differ. The longitudinal course of the stimulation effect will be described using all TQ measurements, including measurements at 2 and 16 weeks. Secondary efficacy measures will be analysed similarly. Only the tinnitus change cannot be divided by a baseline value and will be analysed by ordinal logistic regression as it is ordinal. The daily measurements on visual analog scales will be shown in diagrams. Confidence interval computations will assume normality of logit-transformed VAS. The routinely sampled safety data will all be plotted for each patient and will be used to quantify intensity and duration of adverse effects should such occur. Data analysis will be performed in the Department of Medical Biometry of University Hospital of Tübingen using JMP 7.0 (SAS Institute Inc.) after imputation with SPSS 17.0 (SPSS Inc.).

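### The 75% rule drops imputation at the visits with most missing TQ, leaving completers only, and the two-visit ANOVA lists no patient term

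*Protocol article*

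**What the plan says.** All places are in the protocol article.

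- **Data sets.** Efficacy is analysed mainly per protocol, with intention to treat as exploratory. The rule for missing values is "Missing observations are imputed using a full conditional Markov-Chain Monte Carlo method for variables with more than 75% valid values". No method is named for a variable at or below that limit.
- **Data analysis, weeks 4 and 6.** "The confidence intervals for ratios of geometric means of tinnitus scores at 4 and 6 weeks will be computed from an analysis of variance", and the model is specified "with factors *group *(SAC, TAC, PLC) and *time *(4 and 6 weeks) and the *group*time *interaction". No patient factor appears in the list.
- **Data analysis, later visits.** "Further ANOVAs of TQ with the between subject factor *group *will be carried out after 8, 28, and 56 weeks after the first treatment". Weeks 28 and 56 are also the last two steps of the ordered sequence of tests.
- **Data analysis, other TQ scores.** Scores at 2 and 16 weeks are collected and used only to describe the course over time.
- **Data analysis, software.** Imputation is done in SPSS and analysis in JMP. The number of imputed data sets and any pooling are not mentioned.
- **Sample size calculation.** Log ratios to baseline are assumed to follow "normal distributions with standard deviation 0.18 after taking logarithms", with a relevant effect of 0.19 log units and a local significance level of 0.017.

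**The concern.** The two issues concern different visits.

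**Cut-off.** A variable with 24% missing is imputed and one with 25% missing is not. Protection against selective dropout is thus withdrawn where dropout is heaviest, most plausibly at the long follow-ups. A one-visit ANOVA with group as its only factor cannot use a dropout's earlier TQ scores. If patients who respond poorly leave more often, and more often in one arm, the completers' comparison is biased. Weeks 28 and 56 carry formal tests, so this affects inference and not only description.

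**Two-visit ANOVA.** Each patient contributes a score at week 4 and another at week 6. With the listed factors alone, these count as independent: 2 × 48 = 96 values less 6 cell means leave 90 residual degrees of freedom from 48 patients. The question is which results of that model are harmed.

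**Working it through.** **Inputs from the article:** 48 patients, 16 per arm, SD 0.18 (log ratio), local level 0.017, and effect ln(0.97/0.80) = 0.193, which reproduces the stated 0.19.

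**Assumed, because the article gives no value:** missing rates, the dropout mechanism and the correlation between visits.

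**1. When the cut-off triggers.** More than 75% of 48 means at least 37 valid scores, so 12 missing switch imputation off. In a per-protocol set of 40, 10 missing suffice (30/40 is exactly 75%). The binomial probability of 12 or more missing among 48 is:

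| Assumed missing rate | Chance that the visit is not imputed |
|---|---|
| 10% | 0.2% |
| 15% | 4.8% |
| 20% | 24% |
| 25% | 56% |
| 30% | 82% |

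**2. Complete-case bias if it triggers.** Assume logistic dropout with log-odds rising by 1 per SD of the earlier score, set to give 35% dropout in sham and 15% in each active arm. The completers' mean earlier score then falls 0.292 SD below the full arm's mean in sham and 0.133 SD in active. The bias in the late sham-minus-active difference is 0.18 × r × (0.292 − 0.133):

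| Correlation r | Bias (log units) | Share of 0.19 |
|---|---|---|
| 0.5 | 0.014 | 8% |
| 0.7 | 0.020 | 11% |
| 0.8 | 0.023 | 12% |

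Sham loses more of its high scorers, so it looks better than it is and the treatment effect shrinks. The standard error of the completers' contrast is 0.18 × √(1/(16 × 0.65) + 1/(16 × 0.85)) = 0.074, so the bias is below a third of one standard error. Adjusting for the earlier score among the same completers brought the bias to essentially zero.

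In this scenario the expected number missing is 16 × 0.35 + 32 × 0.15 = 10.4 (21.7%), and the chance of 12 or more is 0.34. The bias is the average at these dropout rates, not the average over only those trials where the cut-off triggers.

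**3. ANOVA without a patient term.** Let σ² be the total variance, r the correlation between weeks 4 and 6, and n = 16.

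- *Contrast at one week.* The true variance is 2σ²/n. The residual mean square estimates σ², so the standard error is right and only the degrees of freedom are too many. Simulated error at nominal 0.017, for r from 0.5 to 0.9, is 0.017 to 0.0195.
- *Group effect averaged over both weeks.* The true variance of an arm mean is σ²(1 + r)/(2n), but the model uses σ²/(2n). Its standard error is 1/√(1 + r) of the true one: 0.82 at r = 0.5 and 0.73 at r = 0.9.
- *Group-by-time contrast.* The true variance is 4σ²(1 − r)/n, but the model uses 4σ²/n. Its standard error is 1/√(1 − r) times too large: 1.4 at r = 0.5 and 3.2 at r = 0.9.

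Simulated error rates (40,000 null trials, F tests at nominal 5%):

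| r | Averaged group effect | Group-by-time |
|---|---|---|
| 0.5 | 13.3% | 0.34% |
| 0.7 | 17.1% | 0.02% |
| 0.8 | 18.7% | 0 |
| 0.9 | 20.7% | 0 |

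For one pairwise contrast averaged over both weeks, at nominal 0.017, the error is 0.050 to 0.085. Accounting for the patient returns it to 0.016 to 0.017.

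**The case against.** Several arguments limit the point, and most of them stand.

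- **The cut-off may never trigger.** A reader might infer that the late visits will be complete-case. The article does not support that: it states no dropout rate, and even in the scenario above about two thirds of trials would still impute. This stands.
- **The bias is modest and away from the primary endpoint.** It concerns weeks 28 and 56, while the primary outcome is TQ after 4 weeks. In the assumed scenario it works against the treatment. This stands.
- **Per-protocol analysis may remove early leavers anyway.** Patients excluded during treatment may not be in the analysis set, so the imputation rule would not govern them. That is plausible, but it does not cover patients who complete treatment and are lost in the long follow-up.
- **The confidence intervals at weeks 4 and 6 are not wrong.** A reader might infer that they are, because no patient term is listed. With the interaction in the model, the planned intervals are most naturally week-specific contrasts, and these are nearly exact. The article names neither an averaged group test nor an interaction test as a planned inference. A factor list in a condensed article also does not prove that patient was left out. This stands.
- **The later ANOVAs need no patient term.** Read as one per visit, they have one score per patient, and separate models fit the article's expectation of differing residual variances. This stands, but a mixed model can also carry time-specific variances.
- **Imputed values are not shown to be treated as observed.** A reader might infer a single imputed data set from the move between packages. The article never says so, and the number of imputations and pooling are details that a condensed article commonly leaves to the full plan. This is not part of the finding.

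What remains is a stated rule that stops imputation where it is most needed and names no fallback, and a two-visit model whose listed factors ignore the pairing of scores within patients.

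**Conclusion.** The point holds in a limited form.

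**Cut-off.** Once 25% or more of the TQ scores at a visit are missing (12 of 48), the stated plan leaves a completers-only ANOVA and discards usable earlier scores. Under the assumed unequal, score-related dropout, the bias is about 0.014 to 0.023 log units, toward a smaller effect, and the rule triggers in about a third of trials. Other dropout patterns would change the size and could change the direction. If values are missing completely at random there is no bias, only loss of precision.

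**Two-visit ANOVA.** The week-specific comparisons can be relied on. A group effect averaged over weeks 4 and 6 from the model as listed could not be: it would reject in 13 to 21% at nominal 5% for correlations of 0.5 to 0.9. The group-by-time test would have almost no power against modest interactions. Neither is a named inference, so this matters only if such output is reported or if the interaction guides whether the weeks are combined.

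The primary 4-week comparison is little affected by either issue, unless a quarter of its own scores are missing.

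**What to change.** Replace the 75% cut-off and the separate ANOVAs by one mixed model on all observed log TQ values from week 2 to week 56.

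- Fixed effects: group, time, group-by-time and log baseline TQ.
- Within-patient covariance: unstructured, or a patient random effect with time-specific residual variances.
- Results: the ratio of geometric means between groups at each week, tested in the order already fixed.

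The model uses dropouts' earlier scores, handles the two scores per patient at weeks 4 and 6, and needs no imputation of TQ follow-up scores. Its protection holds when dropout depends on observed scores.

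If imputation is kept, drop the cut-off, include group and all TQ visits in the imputation model, and pool the results over several imputed data sets. In the two-visit ANOVA, state the patient term.

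The cost is revised analysis wording and a little programming, with no new data. With seven post-baseline visits (2, 4, 6, 8, 16, 28 and 56 weeks), an unstructured covariance has 7 × 8/2 = 28 parameters. With 48 patients it may not converge, so a simpler structure should be named in advance as the fallback.

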### Screening

Patients will be recruited via announcement in the local press, the tinnitus outpatient clinic at the Department of Psychiatry and Psychotherapy, and the outpatient clinic of the Department of Otorhinolaryngology of the University Hospital of Tübingen. A psychiatrist and an otolaryngologist will assess the eligibility according to the inclusion and exclusion criteria listed above.

### Baseline assessments

The detailed time course and plan of the study is displayed in Table 1.

**Table 1 T1:** Time course of the study

Investigation	Screening	Baseline	Treatment				Follow-Up				
			
			2 weeks		2 weeks		11 months				
Visit #	V0	V1	V2-10	V11	V12-20	V21	V22	V23	V24	V25	V26

informed consent	×										

demograph. data	×										

inclusion/exclusion criteria	×										

randomization		×									

ENT investigation/tinnitus localization		×									

audiogram/speech audiometry		×		×		×					

STI		×									

cTBS treatment SAC, TAC, PLC			×	×	×	×					

documentation of side effects			×	×	×	×					

TQ		×		×		x *	×	×	×	×	×

VAS (distress, loudness)		×	×	×	×	×	×	×	×	×	×

VAS (change)				×		×					

SCL-90R		×		×		×	×	×	×	×	×

BDI		×		×		×	×	×	×	×	×

*primary outcome measure

• Ear Nose and Throat (ENT) examination and audiological assessment including

- Standard pure tone audiometry

- Speech audiometry in quiet (mono- and multi-syllables, "Freiburger speech test")

- Hearing in noise test ("Oldenburger sentence test") [42]

- Audiological tinnitus matching

• Structered Tinnitus Interview (STI) [43]

• Tinnitus Questionnaire (TQ) [44,45]

• Visual Analogue Scales (VAS) for tinnitus loudness and annoyance [46]

• Beck Depression Inventory (BDI) [47]

• Symptom checklist 90-revised (SCL-90R) [48].

### Safety

Safety measures are pure tone and speech audiometry as well as speech understanding in noise tests (at Baseline, after 2 weeks of treatment and after the end of the treatment). Adverse events are assessed daily and documented according to the GCP guidelines. Safety and adverse events will be reported together with the results. The occurence of possible adverse effects will be reported in a case report form and handled in compliance with GCP. Study monitoring is provided by CenTrial (Tübingen, Germany).

### Outcome measures

The primary efficacy measure in the present study is the change of the tinnitus distress as measured by the TQ [45] after 4 weeks of cTBS. The TQ [45]), originally developed by Hallam et al. [49], is the most widely used, well validated and reliable inventory [50] to quantify tinnitus ditress available in German language [30,32,34,41,51-58]. It comprises 52 multi-scaled items in order to assess emotional and cognitive handicaps, penetrance of the tinnitus, hearing problems, sleep disturbances, and somatic discomfort. The TQ was used in pharmacological, behavioural and TMS studies. Pharmacological studies did not yield therapeutic effects [58,59]. Behavioural therapy yield effect sizes between 6 and 28% on the TQ [60,61]. Pilot rTMS studies reported effects sizes between 5 and 25% [34,41,52].

Secondary efficacy variables are tinnitus change [46] and the changes in BDI [47] and in the VAS for tinnitus loudness and tinnitus annoyance [46,62].

Changes regarding psychopathology will be measured using the SCL-90R [48]. Feasibility of the study will be assessed and reported together with the results.

### Follow-up assessments

Duration of treatment effects will be measured (TQ, VAS, BDI) 6, 8, 16, 28, and 56 weeks after the first stimulation. Furthermore, 6 months after the end of treatment patients will be asked to report if they regard the estimated benefit as worth the effort.

### Withdrawal from the study

In case of endangerment of personal security or lack of compliance or withdrawal of informed consent, a patient will instantly be excluded from further participation in the study.

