## Discussion

The available data on the efficacy of tinnitus treatment with rTMS is incomplete [30-37]. The effect size, the clinical relevance and the optimal stimulation parameters are virtually unknown. This placebo-controlled phase II clinical trial has been designed to investigate the efficacy of a 4 weeks treatment with bilateral cTBS on chronic tinnitus and to compare the effectiveness of two different stimulation areas. Since the laterality of tinnitus-related cortical hyperactivity and rTMS effects in mono- and bilateral tinnitus have been shown to be interindividually variable [11,64], we opted for a bilateral cTBS. Recent studies on therapeutic efficacy of rTMS in major depression pointing towards a superior effectiveness of longer treatment durations [23] prompted us to extend cTBS treatment to 4 weeks. Moreover, against the background of a dose dependency of rTMS effects in tinnitus [11] and in order to assure a sufficient dose of stimulation, the patients will receive two stimulation trains on each side. Hence, bilateral, long-term application of cTBS to two different cortical sites will provide comprehensive data for an evaluation of the clinical relevance of TMS treatment in chronic tinnitus and an improvement of treatment parameters. Based on the effect size and standard deviation of the Intention-to-Treat analysis as well as on the finding of the optimal stimulation localization a larger clinical efficacy study will be designed.

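### Exclusion for non-compliance or safety ends assessment as well as stimulation, so the ITT estimate meant to plan the next trial rests on imputed outcomes for those patients

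*Protocol article*

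**What the plan says.** The section on withdrawal names three reasons: endangerment, non-compliance and withdrawn consent. All three have the same consequence: "lack of compliance or withdrawal of informed consent, a patient will instantly be excluded from further participation in the study". No section shown provides for assessment after stimulation has ended early.

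The Data sets section makes per protocol the main efficacy set and adds a second analysis: "An exploratory analysis of all dependent variables by the randomised treatment, i. e. the mere intention to treat (ITT), will be conducted", with the stated purpose of planning confirmatory studies. On missing data it says: "Missing observations are imputed using a full conditional Markov-Chain Monte Carlo method for variables with more than 75% valid values". The Data analysis section places this imputation before the analysis. The Discussion then gives the basis for the larger trial: "Based on the effect size and standard deviation of the Intention-to-Treat analysis", together with the choice of stimulation site.

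The primary outcome is the change in TQ after 4 weeks (Outcome measures; V21 in Table 1). For later visits: "Duration of treatment effects will be measured (TQ, VAS, BDI) 6, 8, 16, 28, and 56 weeks after the first stimulation". Audiometry for safety is scheduled at baseline, at 2 weeks and at the end of treatment (Safety; Table 1).

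**The concern.** Only withdrawn consent obliges the trial to stop collecting data. The rule extends the same consequence to patients who comply poorly and to those stopped for safety, two groups whose response or tolerability may well differ from the rest. Stimulation on every working day for four weeks makes some non-compliance foreseeable.

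ITT and per protocol differ largely through such patients. If their later outcomes are not observed, the ITT analysis loses much of the information it is there to provide. At stake is the effect size and SD carried into the next trial. Safety follow-up is also thinner: read literally, a patient removed for endangerment misses the audiometry still to come, although the article's general handling of adverse events under GCP may soften this.

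**Working it through.** **1. What an excluded patient contributes (Table 1).**
- Excluded before V11: baseline TQ and the daily VAS so far. TQ at 2 weeks, 4 weeks and follow-up is missing.
- Excluded after V11 but before V21: baseline and 2-week TQ and the daily VAS so far. TQ at 4 weeks and follow-up is missing.
- Excluded after V21: the primary outcome is observed and only later follow-up is missing.

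**2. Reach of the imputation rule.** More than 75% of values must be valid. With 48 patients, 11 missing leaves 37/48 = 77.1%, which is imputed. With 12 missing, 36/48 = 75.0%, which is not. Three lost in every arm leaves 39/48 = 81%, inside the limit.

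**3. The plan's effect size.** From the Sample size calculation, ln(0.97/0.80) = 0.193, which agrees with the stated 0.19 log units. The stated SD is 0.18, with 16 patients per arm.

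**4. Upper-end illustration.** Assumptions, none of them from the article: *k* of 16 active patients are excluded before V21; they have no benefit, so their mean equals the sham mean; and they are imputed at the full effect seen in those who stay.

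True ITT effect = (16 − k)/16 × 0.19. Reported effect = 0.19. Overstatement = 16/(16 − k) − 1. Because sample size is proportional to 1/effect², the next trial would need (16/(16 − k))² times its planned patients, with the SD held at 0.18.

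| k | True ITT effect | Overstatement | Patients needed / planned |
|---|---|---|---|
| 1 | 0.178 | 6.7% | 1.14 |
| 2 | 0.166 | 14.3% | 1.31 |
| 3 | 0.154 | 23.1% | 1.51 |

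If excluded patients were not imputed but dropped from the ITT analysis, the estimate would again be the effect in those who stayed, with the same figures. The article does not say whether the imputation covers them.

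**5. A milder case.** Take k = 3, all excluded after V11, and assume that half the effect is normally visible at 2 weeks (0.095), that these patients show none of it, and that the regression slope from week 2 to week 4 is 0.7. They are then imputed at 0.19 − 0.7 × 0.095 = 0.1235. The ITT estimate is (13 × 0.19 + 3 × 0.1235)/16 = 0.1775. Against 0.1544 this is 0.1775/0.1544 = 1.15, or 15% too large, and 1.15² = 1.32 times the planned patients. Earlier TQ and VAS data reduce the bias but do not remove it, and they help less for a patient excluded before V11.

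**The case against.** A reader might infer that the outcomes of excluded patients are never measured, that no ITT effect can be obtained, or that ITT collapses into per protocol. The documents support none of these.

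- The rule stops further participation. It does not discard data already collected, and a patient excluded after V21 has the primary outcome.
- Imputation is planned, and even three lost in every arm stays within its limit. An ITT figure can be computed, and the imputation may draw on earlier TQ and VAS.
- The article gives stimulus placement as a particular reason for using per protocol. Patients whose placement deviated but who were not excluded would still separate the two sets.

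Three further objections carry weight. The main efficacy analysis is per protocol, and patients excluded for non-compliance would not ordinarily enter it even if they were followed. The article does not define lack of compliance; if it includes refusing visits or questionnaires, continued follow-up would recover less. A full protocol, not shown, may define the term or provide an assessment at withdrawal.

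These points limit the finding without removing it. The exclusion rule is stated outright, with no exception for assessment. Imputation after exclusion has no observed off-treatment outcomes to learn from, so it must rely mainly on patients who stayed.

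**Conclusion.** The point holds in limited form and is worth correcting. As written, the withdrawal rule does not fit the use that the Data sets section and the Discussion make of the ITT result. For patients excluded before V21, the ITT effect and SD would rest on modelled rather than observed 4-week and later outcomes, with a risk of overstating the effect.

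The size cannot be determined from the article, which gives no non-compliance rate. The 7% to 23% overstatement and the factor of about 1.14 to 1.5 are upper-end figures for 1 to 3 exclusions among 16 active patients. They depend on zero benefit in those who stop and on imputation at the full complier effect; milder assumptions give less. The factor also holds the SD fixed, although a mixture of patients with and without benefit would vary somewhat more.

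The harm falls on the exploratory ITT estimate, on planning of the next trial and, to a lesser degree, on safety follow-up. The trial's per-protocol efficacy conclusion does not change.

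**What to change.** Reconcile the withdrawal section with Data sets, Follow-up assessments and the Discussion by separating the end of stimulation from the end of assessment. State that patients who stop or miss stimulation, but have not withdrawn consent to data collection, stay in the study for the scheduled TQ, VAS and BDI at V21 and V22 to V26, and for the scheduled safety audiometry where feasible. Analyse them in their randomised arm in the ITT analysis. Leave the criteria for stopping stimulation unchanged.

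The cost is a short amendment and a few extra questionnaires and visits, on a schedule and with instruments already in place. Some patients may still decline, so some imputation will remain.
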